**Methods and Design:**

A total of 640 participants (160 in each of four arms) between the ages of 18 and 70 years of age who have low back pain lasting at least 3 months will be recruited from integrated health care delivery systems in Seattle and Oakland. They will be randomized to one of two forms of Traditional Chinese Medical (TCM) acupuncture needling (individualized or standardized), a "control" group (simulated acupuncture), or to continued usual medical care. Ten treatments will be provided over 7 weeks. Study participants and the "Diagnostician" acupuncturists who evaluate participants and propose individualized treatments will be masked to the acupuncture treatment actually assigned each participant. The "Therapist" acupuncturists providing the treatments will not be masked but will have limited verbal interaction with participants. The primary outcomes, standard measures of dysfunction and bothersomeness of low back pain, will be assessed at baseline, and after 8, 26, and 52 weeks by telephone interviewers masked to treatment assignment. General health status, satisfaction with back care, days of back-related disability, and use and costs of healthcare services for back pain will also be measured. The primary analysis comparing outcomes by randomized treatment assignment will be analysis of covariance adjusted for baseline value. For both primary outcome measures, this trial will have 99% power to detect the presence of a minimal clinically significant difference among all four treatment groups and over 80% power for most pairwise comparisons. Secondary analyses will compare the proportions of participants in each group that improve by a clinically meaningful amount.

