### Data safety monitoring board

The Data Safety Monitoring Board (DSMB) established by the National Center for Complementary and Alternative Medicine to monitor large trials will monitor the progress of the trial and review safety data.

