### Adverse events

Participants will be asked about adverse experiences at each clinic visit and during the 8-week telephone interviews. We will define an adverse experience as any unfavorable and unintended sign, symptom or disease temporally associated with the use of the acupuncture treatments, which could reasonably be related to the procedure. Because acupuncture has relatively short-term physiological effects, we will not report adverse events that first manifest more than two weeks after a participant's final acupuncture treatment (or more than 9 weeks after randomization for the usual care control group). Any adverse event that is life-threatening or results in death, hospitalization, a persistent or significant disability/incapacity, a congenital anomaly/birth defect, or cancer will be promptly reported to the DSMB.

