## Stopping rules

The trial will be stopped if the Data Safety Monitoring Board (DSMB) believes there is an unacceptable risk of serious adverse events in one or more of the treatment arms. No interim analyses of efficacy are planned to there are no formal stopping rules for efficacy or futility.

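### The only adverse-event definition makes possible relatedness to acupuncture a condition of counting, cannot apply to usual care, and leaves unclear whether serious events judged unrelated reach the DSMB

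*Protocol article*

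**What the plan says.** All references are to the protocol article.

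- **Definition (Adverse events).** An untoward, unintended occurrence counts only if it is "temporally associated with the use of the acupuncture treatments, which could reasonably be related to the procedure". This is the only safety definition given. The defined term is *adverse experience*.
- **Window (Adverse events).** "we will not report adverse events that first manifest more than two weeks after a participant's final acupuncture treatment". In usual care the cut-off is instead counted from randomisation and set at 9 weeks. The term here is *adverse event*, which is not defined separately.
- **Serious events (Adverse events).** "Any adverse event that is life-threatening or results in death, hospitalization, a persistent or significant disability/incapacity": these, and events meeting one of the other listed criteria, are to be reported promptly to the DSMB. The term is again *adverse event*, and the sentence contains no relatedness condition.
- **Board's remit (Data safety monitoring board).** The board "will monitor the progress of the trial and review safety data".
- **Stopping rules.** The trial stops if the board believes there is an "unacceptable risk of serious adverse events in one or more of the treatment arms". No efficacy or futility rule exists.
- **Masking.** The Abstract says that Therapists are unmasked. Under Randomization to treatment groups, the specific acupuncture assignment is disclosed to the treating acupuncturist only. Diagnosticians and telephone interviewers are masked.

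**The concern.** Whether an event occurred and whether the procedure might have caused it are separate questions. The definition merges them, so a causality judgement on each single event comes before any comparison of arms. A randomised comparison is useful for safety because it can show an excess that nobody would have attributed to treatment case by case. An unexpected harm is the kind most likely to be set aside as unrelated.

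Three things are at stake. First, the count of events in the acupuncture arms may be incomplete. Second, usual care has no procedure to which an event could be related, so it cannot supply a reference rate under this definition. Third, the board judges serious-event risk by arm, and the section does not settle whether it receives all serious events or only those thought possibly related.

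There is also a possible route to bias between needled and simulated acupuncture. Nothing is inserted in the simulated arm, so someone who knows the arm may find bleeding, infection or local pain less plausibly related there. Participants are masked among the three acupuncture treatments, which makes this safety contrast worth protecting from attribution.

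**Working it through.** The plan states no adverse-event rate or safety calculation, so there is no figure of its own to reproduce. The check is mainly of the text.

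**Step 1: the terms side by side**

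| Place | Term used | Relatedness required? | Can it cover usual care? |
|---|---|---|---|
| Questioning at clinic visits and the 8-week interview; Table 3 | adverse experience | through the definition | interview only, as this arm has no treatment visits |
| Definition | adverse experience | yes | no, there is no procedure |
| Reporting window | adverse event | not stated | yes, expressly |
| Serious-event reporting | adverse event | not stated | not restricted |
| Stopping rules | serious adverse event | not stated | judged by arm |

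**Step 2: two readings**

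*Reading A: the two terms mean the same.* In favour: the second term has no definition, only adverse experiences are described as being collected, and the window is justified by how long acupuncture's physiological effects last, which is a causal argument. Under this reading, serious events judged unrelated fall outside DSMB reporting. The usual-care window is then empty, because nothing in that arm can meet the definition.

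*Reading B: adverse event is the wider term.* In favour: the usual-care window then has content, the seriousness list includes cancer and birth defects, which are hard to attribute to needling within 9 weeks, and the board's remit is unrestricted. Under this reading, serious events are reported whatever their cause. The term that governs the window and the DSMB report is then undefined, and the item collected is narrower than the item reported.

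Each reading leaves a defect, and the text does not choose between them.

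**Step 3: window arithmetic.** Seven treatment weeks plus 2 weeks gives 7 + 2 = 9 weeks, the usual-care figure. The windows are matched, which suggests that usual-care events were meant to be reported and makes the mismatch with the definition plain.

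**Step 4: illustration with assumed rates**

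*Serious events affected by the ambiguity.* Inputs: 3 × 160 = 480 acupuncture-arm participants (Abstract), a 9-week window, and an assumed 5-10% hospitalised per year from any cause.

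- 480 × 0.05 × 9/52 = 4.2
- 480 × 0.10 × 9/52 = 8.3

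Under reading B all of these reach the board. Under reading A only those thought possibly related do.

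*Differential filtering.* Take two arms of 160 with the same assumed true event rate of 10%. Reported count = 160 × 0.10 × share kept as related.

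| Share kept, needled | Share kept, simulated | Counts | Apparent ratio |
|---|---|---|---|
| 100% | 100% | 16.0 v 16.0 | 1.00 |
| 90% | 70% | 14.4 v 11.2 | 1.29 |
| 90% | 50% | 14.4 v 8.0 | 1.80 |
| 70% | 90% | 11.2 v 14.4 | 0.78 |

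The ratio depends only on the two shares, and the document supplies neither. The table shows that the filter could create or reverse a difference. It does not show that it would.

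**The case against.** The strongest objection is to a conclusion that a reader might draw: that serious events judged unrelated are withheld from the DSMB. The document does not say this. Its serious-event sentence covers any adverse event on the list, with no relatedness condition, and the features behind reading B support all-cause reporting. This objection stands. Non-reporting is one reading of two unreconciled terms.

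A second tempting inference is that the filter biases the needled versus simulated comparison. That needs someone who knows the arm to judge relatedness, and the article names no judge. Therapists have limited, largely scripted contact with participants, while the Diagnostician who evaluates each participant at every visit is masked, as are the interviewers. A condensed article may properly leave the assessor's identity to the full protocol, so its absence is not held against the plan. This objection also stands: the route is possible but not shown.

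Third, the clause sets a standard of reasonable possibility, not of established causation, so it may exclude few events. That limits the likely size but does not change the structure of the rule.

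Fourth, comparative safety is not among the stated aims, and no safety test is described. That is true. The stopping rule nevertheless asks the board to judge serious-event risk by arm, so how events are counted in each arm matters.

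None of this answers the two points fixed by the text: relatedness is a condition of the only definition, and that definition cannot apply to an arm for which a reporting window is set.

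**Conclusion.** The point holds as a defect in a stated counting rule and an unresolved ambiguity in reporting. Three things rest on the wording alone:

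- An event judged unrelated is not an adverse experience as defined.
- No usual-care event can meet the definition, yet that arm has a 9-week reporting window.
- The window and the DSMB rule use an undefined term, so it is unclear whether serious events judged unrelated reach the board.

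Differential filtering between arms is a risk that the design permits. Its size and direction cannot be derived from the document. The range of 4.2-8.3 hospitalisations rests on an assumed 5-10% annual rate, and the ratios of 0.78 to 1.80 rest on assumed shares kept. Both are illustrations only. The efficacy analyses are not affected. The change is worth making because it is cheap and protects the comparison of serious events on which the only stopping criterion depends.

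**What to change.** In the Adverse events section:

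1. Use one term throughout, for the definition, the questioning, the window and the DSMB report.
2. Delete the relatedness clause, and the tie to acupuncture treatment, from the definition used to record and count events, so that every unfavourable event within the stated reporting window is recorded in all four arms.
3. Record relatedness as a separate field, judged where possible without knowledge of which acupuncture treatment was given.
4. State that all events meeting the existing seriousness list go to the DSMB by arm, whatever that field says.
5. Summarise all events by arm, with related events as a secondary listing.

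The cost is a few reworded sentences and one extra field on the clinic visit form and in the 8-week interview. More unrelated events will have to be logged, and reported counts will be higher in every arm. Treatment, the seriousness list and the stopping criterion stay as they are.

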### Study treatments

In the three acupoint stimulation groups, participants will be treated twice weekly for the first three weeks, and then weekly for four weeks (a total of 10 treatments over seven weeks). Ten treatments were chosen because over 75% of the acupuncturists we surveyed believed 8 treatments would be necessary to treat chronic back pain [19]. These treatments will be provided at no cost to study participants. Electrostimulation, moxibustion, herbs, and other non-needle treatments and adjuncts will not be allowed in this trial.

All participants will be mailed the Back Pain Helpbook[20]within a week of randomization. This evidence-based manual for self-management of chronic back pain includes information on managing flare-ups, physical activity and exercise, and appropriate life-style modifications. From a practical viewpoint, we thought that giving this book to participants in the usual care group would minimize their disappointment at not receiving acupuncture treatment and would therefore reduce losses to follow-up. From a scientific viewpoint, providing the back-care book to all participants permits assessment of the efficacy of acupuncture beyond educational materials alone.

In our pilot study, we found that we could successfully mask participants to treatment group by using two acupuncturists who have minimal contact with each other: a "Diagnostician acupuncturist" who prescribes an individualized treatment plan at each visit and a "Therapist acupuncturist" who provides the treatment to which the participant was randomized. The Diagnostician acupuncturist will evaluate the participant at each visit using TCM diagnostic techniques and will then write a prescription for an individualized treatment designed to treat the back pain and any underlying TCM "constitutional deficiencies" that could prevent the pain from resolving or give rise to recurrences. A Research Specialist will then accompany the participant from the Diagnostician acupuncturist to the Therapist acupuncturist who will then administer the randomly assigned treatment, interacting minimally with the participant. Only one-third of participants randomized to an acupuncture treatment will actually receive the individualized treatment.

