### Primary measures of efficacy/effectiveness

The modified Roland-Morris Disability Questionnaire will be used to measure back-related patient dysfunction [26,27]. This instrument, which asks 23 yes/no questions, takes approximately five minutes to complete. A composite score is obtained by summing up the number of "yes" responses, so the total scores range from 0 to 23. It has been found to be reliable, valid and sensitive to clinical changes [27-32] and is well suited for telephone administration.

Because there are individuals who are very bothered by even a small amount of pain and others who are not bothered by even moderate pain, our primary measure of symptoms assesses participants' perceptions of the impact of pain on their lives rather merely assigning a pain severity score. Thus, participants will be asked to rate how bothersome their low back pain has been during the past week on a 0 to 10 scale where 0 represents "not at all bothersome" and 10 "extremely bothersome". This measure appears to have substantial construct validity – i.e., it is highly correlated with measures of function and other outcome measures [27].

Both primary outcomes will be measured at baseline and during the 8, 26 and 52 week follow-up interviews. The trial's primary endpoint will be the 8 week follow-up, one week after completion of the 10 acupuncture treatments. All interviews will be conducted using computer-assisted telephone interviews (CATI).

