### Statistical analysis

The power calculations are based on simple comparisons of the follow-up scores at a single point in time (eight weeks after randomization) with adjustment for baseline values using analysis of covariance. We also plan to adjust for other baseline characteristics. In a large randomized trial, baseline values and other covariates are unlikely to differ across randomized groups. However, for continuous outcome data, inclusion of baseline covariates can improve precision of the variance estimate and therefore increase power. The covariates to be used in the final model will be based on past experience and model fit as assessed prior to inclusion of treatment group in the model. We will use the Tukey-Kramer method to adjust for multiple pairwise comparisons [36] across the four groups and allow all pairwise comparisons to be conducted holding the overall α = 0.05 fixed.

We will use an intent-to-treat approach to all analyses, i.e. individuals will be analyzed by randomized group regardless of participation in any treatment sessions. This minimizes biases that often occur when participants not receiving assigned treatments are excluded from analyses. Furthermore, we will adjust for geographic site as a main effect. The standard linear regression model (ANCOVA) is of the form:

*Y*(*t*) = *β*_0 _+ *β*_1 _*Baseline *+ *α*_1 _Grp1+ + *α*_2 _Grp2 + *α*_3 _Grp3 + *θ*^*T *^*z *+ *ε*

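### The adverse-event reporting window ends two weeks after each participant's own last treatment in the acupuncture arms but at a fixed 9 weeks in usual care, so time at risk depends on adherence

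*Protocol article*

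**What the plan says.** The Adverse events section sets two cut-offs in one sentence. For the three acupoint stimulation arms, "we will not report adverse events that first manifest more than two weeks after a participant's final acupuncture treatment". For usual care the limit is a calendar one: "or more than 9 weeks after randomization for the usual care control group". The stated reason is that the physiological effects of acupuncture are short-lived.

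Three other statements matter here.

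- Ten treatments are planned over seven weeks, two a week for three weeks and then one a week for four (Study treatments). The primary endpoint is placed one week after that course ends: "The trial's primary endpoint will be the 8 week follow-up, one week after completion of the 10 acupuncture treatments".
- On collection, the Adverse events section says: "Participants will be asked about adverse experiences at each clinic visit and during the 8-week telephone interviews". Table 3 lists adverse experiences at 8 weeks only, not at 26 or 52.
- An adverse experience is defined as one "temporally associated with the use of the acupuncture treatments, which could reasonably be related to the procedure".

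The cut-off refers to each participant's own final treatment. No clause substitutes the scheduled end of treatment or sets a minimum window for those who leave early.

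**The concern.** The 9 weeks in usual care looks like the 7-week course plus the two weeks allowed after it, so the windows were evidently meant to match. They match only for participants who finish on schedule. Anyone in an acupuncture arm who stops early has a shorter window, and the earlier the stop, the shorter it is. A participant who attends no session has no final treatment, so the rule gives no window at all, although the Statistical analysis section foresees people who attend no sessions. Anyone whose visits run late has a window extending past week 9.

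Time at risk for a reportable event therefore depends on adherence, which is observed after randomization and can itself be affected by how treatment is tolerated. An early leaver may describe an event at the 8-week interview that is then excluded by rule, while the usual care limit at the same date is still open. What is at stake is how the adverse-event proportions by arm can be read. The primary efficacy comparisons are not affected.

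**Working it through.** **Inputs.** Two weeks after the final treatment, and 9 weeks after randomization (Adverse events); the treatment schedule (Study treatments); course completed one week before the 8-week interview (Primary measures of efficacy/effectiveness); last routine inquiry at 8 weeks (Table 3 and Adverse events).

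**Reproducing the plan's figure.** On-schedule completer: 7 + 2 = 9 weeks, equal to the usual care limit.

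**Early leavers.** Window end = week of last treatment + 2. The table places each treatment at the end of its half-week (first three weeks) or week (last four), which puts the tenth at week 7. Collectable but unreported weeks = 8 − window end, or 0 if negative.

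| Last treatment received | Week | Window ends | Share of 9 weeks | Weeks before the 8-week interview that go unreported |
|---|---|---|---|---|
| 1st | 0.5 | 2.5 | 28% | 5.5 |
| 3rd | 1.5 | 3.5 | 39% | 4.5 |
| 6th | 3 | 5 | 56% | 3 |
| 8th | 5 | 7 | 78% | 1 |
| 10th | 7 | 9 | 100% | 0 |

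The exact timing is a convention. If the first treatment falls on the day of randomization, the five window ends become 2, 3, 4.5, 6 and 8 weeks. If a single visit takes place at the end of week 1, its window ends at 1 + 2 = 3. Stopping after visit 1 therefore means about week 2 to 3.

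**Effect on an arm's event count.** The article gives no rate of stopping treatment. Its 10% is loss to follow-up, which is a different quantity. As an assumption, let a proportion p stop at visit 6, with event onset uniform over the 8 weeks in which events are routinely asked about and the same event rate in leavers and completers. The share of the arm's events lost is p × (8 − 5)/8:

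- p = 5%: 0.05 × 3/8 = 1.9%
- p = 15%: 0.15 × 3/8 = 5.6%
- p = 30%: 0.30 × 3/8 = 11%

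Using the nominal 9 weeks instead would give 0.15 × 4/9 = 6.7% and 0.30 × 4/9 = 13%. These overstate the practical loss, because no routine question is put after the 8-week interview. Earlier stopping raises the loss (15% stopping after visit 1: 0.15 × 5.5/8 = 10.3%). Onset clustered around treatment lowers it.

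**The case against.** The strongest defence is that the cut-off follows from the definition. Only events plausibly related to the procedure are sought, acupuncture acts briefly, and a window counted from last exposure is a recognised safety convention. On that view, a new event weeks after a single visit is mostly outside what the trial wants to count. This stands as a reason to keep a two-week window as an exposure-based summary, and it means some of the lost events would not have met the definition. It does not justify setting that window beside an arm counted for a fixed 9 weeks. By giving usual care a limit, the plan shows that it means to report events there as well, even though a definition tied to acupuncture fits that arm poorly.

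Four stronger readings are tempting, and the text does not support them.

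- *The harm that makes people stop is discarded.* The rule drops only events that begin more than two weeks after the last treatment. Harm that leads someone to stop normally appears before or soon after that treatment and is kept.
- *The rule breaks the intention-to-treat commitment.* The Statistical analysis section says "individuals will be analyzed by randomized group regardless of participation in any treatment sessions". Early leavers do stay in their randomized arm, and that sentence does not deal with event windows.
- *Serious events are lost.* The sentence sending them promptly to the DSMB has no time limit of its own. Whether the cut-off applies to them is not stated.
- *The comparison of needling with simulated acupuncture is biased.* That would need different stopping in those arms, for which the article gives no evidence. It also describes no formal between-arm safety test.

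The handling of participants with no visits or late visits may be in the full protocol, which is not shown. The two cut-offs themselves are a stated rule, so the main point does not rest on an omission.

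**Conclusion.** The point holds in a limited form. The two cut-offs agree only for on-schedule completers. For early leavers, events can be collected at the 8-week interview and then left unreported, so adverse-event proportions by arm would rest on adherence-dependent time at risk. For a given early leaver the window falls to about week 5 (stopping at visit 6) or week 2 to 3 (stopping after visit 1), against 9 weeks nominally and about 8 weeks in practice for usual care.

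Across an arm the effect is probably modest, and its true size is unknown. The 5.6% to 11% rests on assumed stopping of 15% to 30% at visit 6, uniform onset over 8 weeks and equal event rates in leavers and completers. The sponsor should change the rule, because the change is cheap and removes the dependence on adherence. Nothing here calls the efficacy analysis into question.

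**What to change.** Amend the cut-off sentence in the Adverse events section so that adverse events in all four arms are tabulated by randomized assignment over one common period, from randomization to the 8-week interview. That interview is the last routine inquiry, so a full 9-week table could not be filled without further data collection. Keep the two-week post-treatment window as a secondary, exposure-based table for the acupuncture arms. State whether any time limit applies to serious events sent to the DSMB.

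The cost is small. The data are largely collected already, and the present rule also needs the time at which an event first appeared, although the article does not say how onset is dated.

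There are two drawbacks. Some events unrelated to treatment will be counted in early leavers. A common period also does not equalize ascertainment: the acupuncture arms are asked at every clinic visit as well as at the interview, whereas usual care has no treatment visits and is in effect asked once. The interview report is therefore the most comparable source across arms, and the difference in how often participants are asked should be stated beside the table.
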